### Descriptive statistics

Dichotomous data and counts will be presented in frequencies. Continuous data will be presented in means with a standard deviation or median value with a range.

### Analyses

All patients will be analysed according to the intention to treat approach. Baseline balance will be assessed based on the following patient factors: APACHE-II score, sex, age, duration of symptoms, previous abdominal surgery and previous biliary history. A significant difference (p-value < 0.05) in any of these factors between the two treatment groups will be considered to be an imbalance, the most important factors being APACHE-II score and age. Although we do not expect this to occur, results within the treatment groups will be stratified according to APACHE-II score and age to assure reliable results.

For nominal data the Chi-Square test will be used. For continuous data and counts the independent sample t-test or one-way ANOVA will be used.

In the interim analysis (after one year) the occurrence of the primary endpoint will be compared between the two treatment groups. After the one year follow up of the last patient is completed primary as well as secondary outcomes will be analyzed and compared.

Results will be presented as odds ratios with a corresponding 95% confidence interval. A two-tailed P < 0.05 is considered statistically significant.

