### Randomisation

Patients will be randomly assigned to group A (laparoscopic cholecystectomy) or group B (percutaneous drainage) as shown in the flowchart (Figure 1). Randomisation is done by the study coordinator or primary investigator using an online generator (ALEA 2.2, Academic Medical Centre Amsterdam, the Netherlands https://nl.tenalea.net/amc/ALEA/). Permuted-block randomisation with varying block sizes with a maximum block size of four patients is used to minimize the occurrence of chance imbalance and preserve unpredictability. The sequence of the different blocks is predetermined by an independent programmer and concealed to all investigators. The blocks are generated separately within the different study sites, so stratification according to hospital can be performed.

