## Statistical aspects

### Sample size calculation

The rates for the primary endpoint: major morbidity, re-intervention and mortality for PC were 6.2, 13.1 and 12.7% respectively in the review and 22.2, 18.5 and 14.8% in our own series. We believe that the 6.2% complication rate in the review is an underestimation of the actual rate, but our own value of 22.2% was based on a retrospective, selected group of patients to undergo PC mostly because of their comorbidity. In these patients the complication rate may very well be higher than in the intended population of the CHOCOLATE trial. We therefore chose to combine both complication rates and use the mean value for our sample size calculation: 14.2%.

Morbidity rates for LC in high risk patients vary greatly in current literature and are mainly based on small, retrospective populations. Mortality rates are described to be around 4.5%. In our own series the complication rate was 13.6% and the mortality rate was 4.3%.

Our endpoint comprises major complications and mortality. These rates cannot be simply added to each other since mortality is in most case associated with major complications. We therefore chose to add intervention rates and complication rates and add up a hypothetical 1% for mortality to ensure that no cases positive for the primary endpoint were missed.

A decrease of the primary endpoint from 28.3% (PC group) to 14.6% (LC group) with power 80%, alpha two-sided 5%, Fisher exact, two proportions, 1:1 randomization can be demonstrated by randomizing 2 × 140 patients (PS Power and Sample Size Calculations, version 2.1.30, February 2003). With an expected loss to follow up of 1%, a total of 284 patients will have to be included in the trial.

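### Balance is judged by baseline p-values and the named primary test is unadjusted; prespecified adjustment for APACHE-II, age and hospital would be better, at a modest gain

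*Protocol article*

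**What the plan says.** All statements are in the protocol article.

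- **Baseline balance (Analyses).** Six factors are examined: "Baseline balance will be assessed based on the following patient factors: APACHE-II score, sex, age, duration of symptoms, previous abdominal surgery and previous biliary history". The rule is: "A significant difference (p-value < 0.05) in any of these factors between the two treatment groups will be considered to be an imbalance". APACHE-II and age are singled out as mattering most.
- **Stratified results (Analyses).** After remarking that imbalance is not expected, the plan says "results within the treatment groups will be stratified according to APACHE-II score and age to assure reliable results". It gives no cut-points, no model and no pooled treatment effect.
- **Test (Analyses).** "For nominal data the Chi-Square test will be used". This covers the composite primary endpoint, which is binary. Odds ratios with 95% confidence intervals are promised, with no mention of adjustment.
- **Randomisation.** "The blocks are generated separately within the different study sites, so stratification according to hospital can be performed". No analysis statement mentions hospital.
- **Data collection & follow-up.** APACHE-II score and age are recorded on admission, so every variable needed for adjustment is in hand.

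**The concern.** Two stated choices work against each other.

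First, if allocation is properly random, every baseline difference is due to chance. A p-value then shows only how unusual the difference is, not how far it shifts the outcome comparison. A non-significant difference in a strong predictor can matter, and a significant one in a weak predictor need not.

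Second, the plan ranks two predictors highest and stratifies allocation by a third variable, then names a primary test that uses none of them. The sentence on stratification does not fill the gap. As worded it describes a breakdown of results inside each arm, not an adjusted comparison between arms. It is also unclear whether the breakdown is always made or only after an imbalance is declared, and how it relates to the primary test.

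At stake are some precision, protection against an unlucky allocation, and clarity about which estimate decides superiority.

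**Working it through.** **1. The plan's sample size.** The inputs are "A decrease of the primary endpoint from 28.3% (PC group) to 14.6% (LC group) with power 80%, alpha two-sided 5%, Fisher exact" and "1:1 randomization can be demonstrated by randomizing 2 × 140 patients". With p1 = 0.283, p2 = 0.146 and mean p = 0.2145, the uncorrected two-proportion formula is

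n = [1.960 × √(2 × 0.2145 × 0.7855) + 0.8416 × √(0.283 × 0.717 + 0.146 × 0.854)]² / (0.283 − 0.146)² = (1.138 + 0.482)² / 0.01877 ≈ 139.7, so 140 per arm.

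With 1% loss, 140/0.99 = 141.4, rounded up to 142; 2 × 142 = 284. This agrees with "With an expected loss to follow up of 1%, a total of 284 patients will have to be included in the trial". By exact enumeration, 140 per arm gives 80.5% power for the chi-square and 76.5% for Fisher's exact test. The figure is therefore a chi-square figure labelled as Fisher. The two sections should be reconciled, but the present point does not depend on it, because both tests are unadjusted.

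**2. How often the baseline rule fires by chance.** For independent tests at 5%:

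- six factors: 1 − 0.95⁶ = 26.5%
- APACHE-II and age only: 1 − 0.95² = 9.75%

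Correlation between the factors would lower both.

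**3. Power and overall type I error.** The documents give no prognostic strengths, so these are assumed. The simulation used 280 patients, 30 hospitals (the number in the Abstract), the plan's event rates and 4,000 runs per setting. The adjusted model contained APACHE-II and age; hospital was examined separately by a Mantel-Haenszel test.

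| Assumed OR per SD, APACHE-II / age; hospital SD (logit) | Power: chi-square | Power: adjusted | Power: Mantel-Haenszel | Null error, same order |
|---|---|---|---|---|
| 1 / 1; 0 | 81.0% | 80.5% | 80.4% | 4.6%, 4.4%, 4.6% |
| 1.3 / 1.3; 0.3 | 81.1% | 81.5% | 80.7% | 4.2%, 4.1%, 4.6% |
| 1.5 / 1.5; 0.5 | 81.1% | 82.2% | 81.6% | 5.2%, 5.2%, 5.6% |
| 2 / 1.5; 0.5 | 80.1% | 83.1% | 80.3% | 4.1%, 4.1%, 4.4% |

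The Monte Carlo standard error of each power is about √(0.8 × 0.2/4000) = 0.6 points. Adjustment gains about 0 to 3 points. Accounting for hospital gains about half a point at most. A stronger predictor gives more: a separate run of 1,500 trials per scenario, with one combined predictor at log-odds 1.0 per SD, gave 84% adjusted against 78–80% crude.

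**4. Type I error given the observed imbalance.** No treatment effect, event rate 21.45%, 140 per arm, one predictor standing for APACHE-II, 12,000 runs; z is the standardised baseline difference.

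| Assumed OR per SD | Baseline difference | Crude | Adjusted |
|---|---|---|---|
| 2 | any | 4.4% | 4.4% |
| 2 | \|z\| 1.28–1.96 (passes as balanced) | 5.9% | 4.3% |
| 2 | \|z\| ≥ 1.96 (617 runs) | 9.7% | 4.7% |
| 1.5 | \|z\| 1.28–1.96 | 5.5% | 4.9% |
| 1.5 | \|z\| ≥ 1.96 (625 runs) | 5.6% | 4.8% |

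In the 617-run row the standard error of the crude figure is √(0.097 × 0.903/617) = 1.2 points. At an odds ratio of 1.5 the gaps are within simulation error.

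**5. Patients per hospital.** 284/30 = 9.5 patients, and 9.5 × 0.2145 ≈ 2 events. That is too few for 30 fixed hospital effects.

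**The case against.** The best defence has four parts.

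- **A condensed article leaves detail elsewhere.** Covariate terms and the handling of strata are often left to a full protocol or analysis plan. Silence about hospital alone would not be a finding. The baseline p-value rule and the chi-square are, however, stated methods, and adjustment would change what is stated.
- **The stratifiers are named in advance.** A reader might infer that the stratification is post hoc and that the primary p-value depends on the baseline data. The text does not support this. APACHE-II and age are fixed beforehand, the sentence can be read as a precaution taken in any case, and nothing says a stratified result replaces the chi-square. What stands is the ambiguity over trigger, cut-points and role.
- **The 26% has no shown consequence.** A reader might infer that a quarter of such trials would have their analysis altered. No response is stated for four of the six factors, and if the stratification is unconditional, neither 26% nor 10% changes anything. The figure shows that the rule is uninformative, not that the result is distorted.
- **The gain is small and assumed.** Eligibility confines APACHE-II to 7–14, which narrows the spread available for adjustment, and calling a factor important does not give its strength. This stands, and it limits the size of the point.

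A reader might also infer that ignoring the hospital strata invalidates the standard error or the test. The simulated null error does not support that.

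**Conclusion.** The point holds as an advisable improvement, not as a threat to validity. Baseline significance is an unsuitable criterion for prognostic imbalance, and the named primary test leaves unused the three variables the plan itself treats as important.

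The crude test remains valid on average: null error was about 4% to 5.6% for all three methods. The cost of leaving the plan as it stands is about 0 to 3 points of power over the main assumed range, almost none of it from hospital. There is also no protection when allocation happens to be unlucky on a strong predictor. The 9.7% against 4.7% contrast applies only when APACHE-II differs significantly, and it needs an odds ratio of 2 per SD; at 1.5 it nearly vanishes.

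Prognostic strengths and between-hospital variation are assumptions, and the 26% and 10% assume independent tests. A single model with APACHE-II, age and a random hospital intercept was not itself simulated; hospital's small contribution is judged from the Mantel-Haenszel results.

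**What to change.** - Delete the baseline significance tests and describe balance only.
- Prespecify one primary comparison between arms: logistic regression of the composite on treatment, adjusted for APACHE-II and age as continuous variables and accounting for hospital, for example by a random intercept. Report the odds ratio and 95% confidence interval already planned.
- Keep the crude chi-square as a sensitivity analysis.
- Label any breakdown by APACHE-II or age as supportive, and say whether it is always produced.

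The cost is a change of wording. The variables are already recorded and the sample size need not change. With 34 patients enrolled at publication, it can be settled well before the final analysis. The one small downside is that the odds ratio becomes conditional on the covariates, whereas the trial was sized on two crude proportions; the retained chi-square keeps that link.

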### Primary & Secondary endpoints

The primary endpoint is a composite endpoint of all major morbidity, re-intervention and mortality. Table 1 provides an overview of the definitions. Complications occurring during the first 30 days subsequent to randomisation and need for reintervention and mortality during the one year follow-up period will be compared.

**Table 1 T1:** Definitions of the primary endpoint.

Endpoint	Definition
*Complications*	
Intra-abdominal abscess	Fever and/or elevated CRP/WBC and intra-abdominal fluid collection on CT-imaging or ultrasound.
Biliary injury	All injuries of the intra- and extrahepatic biliary ducts including leakage of the biliary tree*.
Bleeding	Drop in haemoglobin level requiring transfusion and/or reintervention.
Pneumonia	Coughing or dyspnoea, radiography with infiltrative abnormalities, elevated infection parameters and positive sputum culture.
Myocardial infarction	Symptomatic elevated cardiac enzymes and abnormalities on electrocardiography or cardiac ultrasound.
Cerebrovascular	(Temporary) loss of function of any body part or sense caused by cerebral ischemia or bleeding, proven on cerebral CT imaging.
Thrombo-embolic	Symptomatic deep venous thrombosis or pulmonary embolism, radiologically proven.
*Need for re-intervention*	Relaparoscopy, laparotomy, ERCP, intervention radiology, readmission
*Mortality*	

CRP - C-Reactive Protein; WBC - White Blood Cell count; CT - computed Tomography; ERCP - Endoscopic Retrograde Cholangiopancreaticography

* Type A: leakage of the minor hepatic ducts or cystic duct. Type B: leakage of common bile duct (CBD) without stricture - Type C: stricture of the CBD without bile leakage - Type D: complete transection of the CBD with or without resection of a part of it [11].

The secondary endpoints include all individual components of the primary endpoint and in addition all minor complications including wound infection, bleeding without need for transfusion or intervention and urinary tract infection, difficulty of cholecystectomy (as scored by VAS 1-10), total length of hospital stay, emergency room visits for related medical problems, re-admissions, duration of hospital and intensive care stay and total (direct and indirect) costs.

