### Premature termination of the study

The results of the interim analysis performed after the first year of inclusion will be evaluated by the independent DSMB. The primary endpoint will be monitored for benefit or harm using a restricted procedure (Whitehead, 1997), designed according to the sample size characteristics as described in the protocol. The Peto approach will be followed meaning that the study will only be stopped for beneficial effects in case of a p-value < 0.001.

Safety monitoring will be performed specifically for mortality with a two-sided type I error (α) of 0.05. A relative risk of ≥ 2 will be considered reason to advise to terminate the trial.

The trial will not be stopped for futility, the reason being that this is the first randomized controlled trial on this subject and treatment policy will be based on this trial.

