## Trial status

Approval of the study protocol from the central medical ethical committee as well as all local ethics committees has been obtained. Patients are being included in the trial in all participating centres. Currently 34 patients are enrolled in the CHOCOLATE trial.

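### The efficacy interim is set by calendar at one year, before event-free patients can be classified on a one-year composite, and the two stopping sentences are not reconciled

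*Protocol article*

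**What the plan says.** Under Analyses, the protocol article plans one efficacy look: "In the interim analysis (after one year) the occurrence of the primary endpoint will be compared between the two treatment groups". Premature termination of the study fixes what one year means: "The results of the interim analysis performed after the first year of inclusion will be evaluated by the independent DSMB". The trigger is therefore calendar time from the start of recruitment, with no number of patients or events attached.

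Under Primary & Secondary endpoints, the composite has two windows. One part is "Complications occurring during the first 30 days subsequent to randomisation"; the other is "need for reintervention and mortality during the one year follow-up period will be compared". The Abstract also gives one year for re-intervention and mortality.

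For stopping, Premature termination of the study states: "The primary endpoint will be monitored for benefit or harm using a restricted procedure (Whitehead, 1997"). The procedure is to be designed from the sample-size characteristics. The next sentence invokes the Peto approach, under which "the study will only be stopped for beneficial effects in case of a p-value < 0.001". A separate rule covers mortality, and stopping for futility is excluded.

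Trial status reports: "Currently 34 patients are enrolled in the CHOCOLATE trial".

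**The concern.** A patient randomised in month 8 of recruitment has four months of follow-up at the look. If that patient has had an event, the outcome is known. If not, the outcome is still open for another eight months. Only patients randomised at the very start escape this. The one test the article names for yes/no data is the chi-square, which needs each patient classified.

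Two things are at stake. First, the data safety monitoring board (DSMB) would be handed a difference that need not estimate the one-year effect. The shortfall can differ between arms, because re-intervention makes up a large part of the planned PC rate and no separate part of the planned LC rate. Second, the board would have two sentences about stopping on the primary endpoint and no statement of how they work together.

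**Working it through.** **Inputs.** Planned rates 28.3% (PC) and 14.6% (LC), two-sided 5%, power 80%, 140 per arm, 284 in total (Sample size calculation). 284 patients in two years (Abstract). First randomisation 23 February 2011 (Feasibility). 34 enrolled (Trial status). Publication date 12 January 2012.

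**The plan's own figure.** With pooled variance under the null and no continuity correction:

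n = [1.960 × √(2 × 0.2145 × 0.7855) + 0.842 × √(0.283 × 0.717 + 0.146 × 0.854)]² / 0.137² = 139.7, so 140 per arm, as stated. The rates are built as 14.2 + 13.1 + 1 = 28.3 for PC and 13.6 + 1 = 14.6 for LC.

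**Follow-up available at the look.** Uniform planned accrual gives 284/2 = 142 enrolled at 12 months:
- with at least 30 days: 142 × 11/12 ≈ 130
- with at least 3 months: 142 × 9/12 ≈ 107
- with 12 months: about 0
- mean follow-up: about 6 months

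For actual accrual, 23 February 2011 to publication is 10.6 months. That gives 34 × 12/10.6 ≈ 38 patients at one year. If the count of 34 was taken at 6 months (an assumption), the figure is 68. So the look would have about 38 to 68 patients, or 19 to 34 per arm.

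**Size of the truncation.** Assume that all LC events and the PC complications and mortality increment (14.2 + 1 = 15.2%) are early, and that the 13.1% PC re-interventions spread evenly over the first m months. With uniform accrual over 12 months, the share of re-interventions already seen is 1 − m/24.

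| m (months) | Share seen | PC seen | Difference from 14.6% | Share of 13.7 points |
|---|---|---|---|---|
| 12 | 0.500 | 21.75% | 7.15 | 52% |
| 3 | 0.875 | 26.7% | 12.1 | 88% |
| 2 | 0.917 | 27.2% | 12.6 | 92% |

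**Power to reach p<0.001**, full design effect and complete outcomes, normal approximation:

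Φ{[0.137 − 3.291 × √(2 × 0.2145 × 0.7855/n)] / √[(0.283 × 0.717 + 0.146 × 0.854)/n]}

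- n = 19 per arm: 1.1%
- n = 34 per arm: 2.6%
- n = 71 per arm: 9.3%

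With the m = 12 truncation (21.75% against 14.6%), 71 per arm gives 1.4%.

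**The two boundaries.** Peto is flat: z = 3.29 at any information level. The restricted boundary itself is not in the article. As a stand-in only, a two-look O'Brien-Fleming boundary gives:
- 50% information: z = 1.977/√0.5 = 2.80, p about 0.005, looser than Peto
- 24% (68/284): z = 1.960/√0.24 = 4.00, p about 0.00006, stricter than Peto
- 13% (38/284): z = 1.960/√0.13 = 5.44, p about 0.00000005, much stricter than Peto

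**Type I error.** With p<0.001 at the look and 0.05 at the end, the overall level is 0.0508, 0.0506 and 0.0502 at 12%, 25% and 50% information.

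**The case against.** Several points on the other side stand.

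- A reader might infer that nobody has a usable outcome at the look. That goes too far. Anyone who already has a component event is classified, and most enrolled patients would have passed 30 days. The gap concerns patients without an event.
- A reader might infer that half the effect would be lost. That needs PC re-interventions to spread evenly over a year. The Background's retrospective PC series reports three recurrences and four interval cholecystectomies among 27 patients at a mean follow-up of eight weeks, which makes an earlier concentration plausible.
- A reader might infer that the two stopping sentences flatly contradict each other, or that Peto is five times stricter. Read naturally, the word only makes p<0.001 a necessary condition for a benefit stop, so a p-value between 0.001 and 0.005 does not stop the trial. The factor of five belongs to 50% information. At the 13 to 24% that current accrual implies, the same approximation is stricter than Peto.
- Expected follow-up is equal between randomised arms, so the truncated comparison remains valid under the null. Dilution makes a benefit stop less likely, and futility stopping is excluded.
- Slow accrual is partly addressed under Feasibility: inclusion is assessed after one year and centres can be added. Only 15 of the planned 30 had local approval, so extrapolating from 34 may be pessimistic.

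It can also be said that handling of partial follow-up belongs in a fuller document. That would answer a silence, but here the article itself fixes a calendar trigger for comparing a one-year outcome. The final analysis, by contrast, expressly waits for the last patient's full year.

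**Conclusion.** The point holds in a limited form. At the planned date the one-year composite cannot be determined for almost any patient without an event, so a simple comparison of occurrence is truncated. The apparent difference would be about 7 to 13 points instead of 13.7, depending on an assumed timing of PC re-interventions that the article does not give. The look also has little chance of crossing p<0.001: about 1 to 3% at the accrual implied by 34 enrolled and 9% at planned accrual, both assuming complete outcomes and uniform accrual.

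On the boundaries, two questions are unsettled. Is p<0.001 sufficient for a benefit stop when the restricted boundary has not been crossed? Which boundary governs harm on the primary endpoint?

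Inflated type I error and a compromised final result are not supported. The overall level stays within 0.0502 to 0.0508, and the final analysis uses complete follow-up. The consequence is a poorly informative look with an ambiguous instruction to the DSMB.

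**What to change.** Choose one of two routes for the look, before the interim date.

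1. Replace the calendar trigger by a stated number of patients with completed one-year follow-up.
2. Keep an earlier look, but compare the arms by a method that handles partial follow-up: Kaplan-Meier or log-rank, or events within a fixed early window that all analysed patients have completed.

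In either case, reconcile the two sentences under Premature termination of the study into one stated boundary for benefit and one for harm on the primary endpoint. Keep the six-monthly DSMB safety reviews.

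The cost is protocol and DSMB wording, with no extra patients. Route 1 delays the look. At planned accrual of 142 a year, 71 completers are reached at month 18, with 213 already enrolled, and 142 completers at month 24, when enrolment ends, so a half-information look would save no recruitment. Route 2 needs slightly more analysis work.
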